### Design

The present study is a multicenter randomized stepped wedge trial. Patients with a DRF treated non-operatively and without performance of a closed reduction will be included in the study.

This stepped wedge trial will include 10 clusters, expecting to include 4 patients per cluster per time period of 4 weeks (Table 1). Every cluster will be randomized to a step: the moment when a cluster will start with the study. A transition period of one time period of 4 weeks is added between conditions A and B. This transition period is meant for explaining the treatment and to give instructions to the hospitals and caregivers to re-organize the treatment protocols.

**Table 1 Tab1:** Design Cast OFF-2, stepped wedge design

Cluster	T1	T2	T3	T4	T5	T6	T7	T8	T9	T10	T11	T12
1	A		B	B	B	B	B	B	B	B	B	B
2	A	A		B	B	B	B	B	B	B	B	B
3	A	A	A		B	B	B	B	B	B	B	B
4	A	A	A	A		B	B	B	B	B	B	B
5	A	A	A	A	A		B	B	B	B	B	B
6	A	A	A	A	A	A		B	B	B	B	B
7	A	A	A	A	A	A	A		B	B	B	B
8	A	A	A	A	A	A	A	A		B	B	B
9	A	A	A	A	A	A	A	A	A		B	B
10	A	A	A	A	A	A	A	A	A	A		B

*A*, usual care, 4–5 weeks of plaster cast treatment; *B*, 1 week of plaster cast treatment

An inclusion of 4 patients per cluster per month is expected. Before starting this study, every hospital needs to indicate the number of patients seen per month with a DRF who are treated non-operatively. Hospitals of which the expected number of patients will be less than 4 patients per month will be combined to one cluster. By adapting the study protocol based on the expected available patients, we expect that all clusters will reach sufficient inclusions.

Randomization will be performed to determine when a cluster will start with the study. The study period for every included patient will be 1 year. Follow-up of the included participants is the same for both groups: conditions A and B.

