### Power analysis

We used the stepped wedge sample size tool in STATA.

A sample size of 330 patients was calculated with a power of 0.85, alfa of 0.05, and *ICC* of 0.01. We designed the stepped wedge for ten clusters with three patients per cluster per time period (Table 1). We used results from our pilot study for the reference values. The Patient-Rated Wrist Evaluation (PRWE) scores after 6 weeks were used as this will be one of our most important outcomes and have a validated clinical difference score. We used a PRWE score of 35 for the control group and 25 for the intervention group. A difference of around 10 points is needed to reach a relevant clinical difference [18]. In order to account for a 30% loss to follow-up, we aim for a sample size of 440 patients, i.e., four patients per cluster per time.

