### Randomization

Each cluster will start with the usual care: condition A. The clusters/hospitals will be randomized for when to start with condition B. Patients are not randomized but follow the condition in their hospital. Castor will be used for randomizing the clusters. The clusters will be blinded only for the timing when they will start with the treatment of 1-week plaster cast immobilization: condition B. The researcher who will perform the randomization through castor will let the clusters/hospitals know when to start with condition B. At the beginning of the study, all hospitals will be informed about when they will switch from condition A to B. The data analysts will be blinded for the randomization of the clusters and when every cluster starts with condition B.

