### Statistical analysis

Descriptive analyses with median, range, and percentage will be used to describe demographic variables and outcomes such as age and gender. We will analyze the percentage of protocol violations and the willingness to participate from participating patients, hospitals, and physicians using a feedback evaluation. Patients will be asked to give feedback at the end of their follow-up period and physicians will be asked feedback after 6 months and 12 months.

A multivariate linear regression mixed model will be used to analyze the data from the different randomization groups and to account for clustering of repeated measurements within patients and within hospitals and time. We will analyze the effect of the intervention, in comparison with the usual care, on the PROs, return to activity, pain scores, and complication rate. We will adjust for confounding factors such as age, gender, and clinical parameters. The difference in complication rate will be determined using either a Fisher exact or a chi-square test, depending on the order of magnitude of the results. The difference in PCS-4 score, VAS score, and patient satisfaction will be determined using a *t*-test. The analysis will be performed by using the intention-to-treat model (according to the groups to which they were originally designed).

A cost-effective analysis will be performed additionally to the above-mentioned analyses. A budget impact analysis will be performed from various perspectives with the budgetary framework for the care as the base case perspective.

For missing data from patients who fulfilled the study, the available data will be analyzed if possible, for any interesting findings, and otherwise, the missing data will be imputed with replacement values using multiple imputation analysis.

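### PCS-4, VAS, satisfaction and complications are given plain tests that ignore calendar time and cluster, beside an overlapping mixed model, with no word on which analysis counts

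*Protocol article*

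**What the plan says.** The Statistical analysis section of the protocol article first names a linear mixed model, intended to "account for clustering of repeated measurements within patients and within hospitals and time". The next sentence says that the intervention effect will be analysed "on the PROs, return to activity, pain scores, and complication rate".

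Two further sentences then assign simple tests to some of the same outcomes. "The difference in complication rate will be determined using either a Fisher exact or a chi-square test", depending on the size of the numbers. For three more outcomes, "The difference in PCS-4 score, VAS score, and patient satisfaction will be determined using a" t-test. Nothing marks these tests as descriptive or supportive, and nothing says which result counts when an outcome falls under both.

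The design is described elsewhere. Under Randomization: "Patients are not randomized but follow the condition in their hospital". Under Design: "This stepped wedge trial will include 10 clusters, expecting to include 4 patients per cluster per time period of 4 weeks", and "A transition period of one time period of 4 weeks is added between conditions A and B". In Table 1 every cluster is under condition A (usual care) in T1, and every cluster is under condition B (1-week cast) in T12. The Power analysis section uses a stepped-wedge tool: "A sample size of 330 patients was calculated with a power of 0.85, alfa of 0.05, and" an ICC of 0.01.

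**The concern.** In a stepped wedge, condition is tied to calendar time by design: A patients come early and B patients late. A test on pooled A versus B patients has no term for calendar period. Any change over the year in case mix, season, aftercare or pain reporting is therefore counted as an effect of the 1-week cast. Such a test also treats patients of the same cluster as independent. The sample size was derived with a stepped-wedge method, so these tests depart from the trial's own design basis.

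The second problem is precedence. VAS and complications, and satisfaction and PCS-4 if counted as patient-reported outcomes, can end up with two analyses that may disagree. The Hypotheses section predicts lower pain scores and no difference in complications, so these results will be read as conclusions. A time trend could create a difference or hide one.

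**Working it through.** **Inputs.** From the protocol: the layout of Table 1 (10 clusters, 12 periods, one transition period per cluster), 3 patients per cell in the power calculation and 4 planned, ICC 0.01, alpha 0.05 (taken as two-sided), and PRWE 35 versus 25. Not in the protocol, hence assumed: any drift over time, ICCs above 0.01, complication rates, and the SD.

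**The plan's own figure.** Each cluster has 11 counted cells, 110 in all (55 A, 55 B). 110 × 3 = 330 and 110 × 4 = 440, as stated. In a generalised least squares calculation with fixed periods and a random cluster effect, the SE at 3 per cell and ICC 0.01 is 0.1669 SD. The stated power follows if the SD is 20: 10 / (0.1669 × 20) = 2.996, and Φ(2.996 − 1.960) = 0.85. The SD was solved from the power, so this match depends on it.

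**Time gap.** Cluster k is under A in T1 to Tk. The mean A period is Σk(k+1)/2 over k = 1 to 10, divided by 55, which is 220/55 = 4.0. By symmetry the mean B period is 13 − 4.0 = 9.0. The gap is 5 periods, or 20 weeks. A linear drift of x per period shifts the unadjusted B − A difference by 5x. A total drift D over T1 to T12 (11 steps) shifts it by 5D/11.

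**Clustering alone (SD units, 220 per condition).**
- SE assumed by the t-test: √(2/220) = 0.0953.
- Cluster k holds k/55 of the A patients and (11−k)/55 of the B patients. The sum of squared differences in these shares is Σ(2k−11)²/55² = 330/3025 = 0.1091.
- True SE of the unadjusted difference at ICC 0.01: √(0.99 × 2/220 + 0.01 × 0.1091) = 0.1005.
- Ratio 1.054; at 165 per condition it is 0.1144/0.1101 = 1.039.

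**Type I error of the nominal 5% t-test.** With s₀ the t-test SE, s the true SE and b = 5D/11, it is Φ(−1.96 s₀/s + b/s) + Φ(−1.96 s₀/s − b/s).

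| N | ICC | no drift | D = 0.2 SD (b = 0.091) | D = 0.5 SD (b = 0.227) |
|---|---|---|---|---|
| 440 | 0.01 | 6.3% | 17.3% | 65.6% |
| 330 | 0.01 | 5.9% | 14.1% | 54.0% |
| 440 | 0.05 (assumed) | 11.5% | 21.9% | 63.3% |
| 440 | 0.10 (assumed) | 17.6% | 26.6% | 61.6% |

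Simulation of the first row (8,000 runs) gave 6.4%, 17.1% and 65.1%.

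**Complications.** Chi-square test with no true effect, 220 per condition, ICC 0.01, 4,000 runs: about 6% rejections with a flat 15% rate, 13% if the rate drifts from 15% to 10%, and 29% if it drifts from 20% to 10%.

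**Precision of the adjusted estimate.** At ICC 0.01 the SE with cluster and period in the model is 0.1467 at N = 440 (0.1467/0.0953 = 1.54 times the t-test SE) and 0.1669 at N = 330 (0.1669/0.1101 = 1.52 times).

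**Sparse events.** At 3 analysed patients per cell, T1 and T12 hold 30 patients each and the other ten periods 27 each. Treating patients as independent, the chance that at least one period has no complication is 1 − (1 − 0.95²⁷)¹⁰(1 − 0.95³⁰)² = 0.965 at an assumed 5% rate. At 10% it is 0.496. A period without events has no finite maximum-likelihood effect in a logistic model.

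**The case against.** The strongest reply is that the section already has a suitable model. It places pain scores, complication rate and patient-reported outcomes under a mixed model that allows for hospital and time. A reader might infer from the t-test sentence that these outcomes get no adjusted analysis. The text does not support that: the fault is two analyses without an order of precedence. Nor does it follow that the two p-values will conflict; they may agree.

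A reader might also take the ratio of about 1.5 to mean that the t-test understates its own error by half. It does not. That ratio compares two different estimators and is the price in precision of adjusting for period. The t-test's own SE is only 4 to 5% too small at the one ICC that the protocol gives.

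Nor do the documents show that bias is present. The high error rates rest on assumed drifts. At the back-solved SD of 20, a drift of 0.5 SD is 10 points, as large as the PRWE effect used for the sample size (35 versus 25).

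Finally, the outcomes concerned are listed as secondary at the start of Methods. The PRWE, which drives the sample size, is not assigned to a plain test. How time enters the mixed model, and at which level the random effect sits, can be left to an analysis plan that is not shown.

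All of this limits the size of the point. It does not remove it: the simple tests are stated as the way the differences will be determined, and an analysis plan that follows the protocol would carry them forward.

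**Conclusion.** The point holds in this form: the Statistical analysis section assigns overlapping outcomes to a mixed model and to plain tests without saying which counts, and the plain tests are wrong for this design. The 20-week gap and the bias of 5x per unit of drift follow from Table 1 alone. Clustering by itself matters little at ICC 0.01, with a type I error of about 6%. The larger exposure is the missing period adjustment: about 17% and 66% at N = 440 under assumed drifts of 0.2 and 0.5 SD over T1 to T12. The true drift is unknown and may be nil. The finding does not reach the PRWE comparison. It should still be corrected before analysis, because pain and complications carry stated hypotheses and the correction is a matter of wording.

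**What to change.** Delete the t-test and Fisher/chi-square sentences, or label those tests descriptive.

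For PCS-4, VAS and satisfaction, make one model the sole inferential analysis: a mixed model with fixed calendar-period effects, a random effect for the randomised cluster, a random patient effect, and a small-sample correction for ten clusters.

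For complications, use a binary-outcome version: a logistic mixed model, or GEE with a small-sample correction. If events are sparse, enter calendar time in a coarser or smooth form, since separate effects for all twelve periods may not be estimable.

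Do not add the VAS at inclusion as a covariate unless it is shown to be measured before the conditions diverge. Under Patient selection and methods, consent is sought at the 1-week visit, and under Investigational treatment that is the visit at which condition B patients have the cast removed.

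The cost is one reworded paragraph, slightly more analysis work, and wider confidence intervals (SE about 1.5 times that of the t-test at ICC 0.01). Data collection does not change.

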## Background

The distal radius fracture (DRF) is a common fracture. A large part of all diagnosed fractures at the Emergency Department are DRFs, around 17%. One-third of these fractures are non-displaced fractures [1–3].

In recent years, there has been an increased interest in the treatment of DRFs, caused by the increasing prevalence of DRFs and improvements in minimal invasive surgical treatment techniques. However, recent literature mainly focused on treatment options for unstable distal radius fractures, for which several treatment modalities have been advocated [4, 5]. Nonetheless, little attention has been paid to the treatment of the stable DRF. To date, there are only a few studies that have investigated the duration of immobilization for non-operatively treated, stable DRFs [6]. A systematic review (2018) included 12 studies, of which a small part focused on non-reduced fractures. The authors concluded that an immobilization period of 3 weeks or less is equally effective compared to the longer immobilization period and might be associated with better functional outcome [6].

There are several guidelines in the world for DRFs [4, 7]. However, a unified treatment recommendation for non-reduced (minimal and non-displaced) DRFs does not exist. The usual care in the Netherlands consists of 3- to 5-week immobilization for these kinds of fractures. There are several studies that show that the 1 week of plaster cast treatment for a stable DRF is safe and effective [6, 8, 9]. A feasibility study including 40 patients with a non-reduced DRF, randomized in an intervention group (1 week of plaster cast treatment) or control group (4–5 weeks of plaster cast treatment) showed positive results and no secondary displacement. In addition, a trend was shown in the intervention group of having less pain, better functional outcome after 6 weeks, going back to work earlier, higher patient satisfaction, and no differences in complications. Moreover, it appeared that patients preferred a shorter immobilization period (cross-over in eight patients, seven patients went from the control group to the intervention group) [10].

Recent studies have shown that a long period of immobilization is associated to more post-traumatic pain by increasing disuse and kinesiophobia [11–13]. These studies also show that early mobilization after a period of plaster cast may reduce the incidence of post-traumatic pain including complex regional pain syndrome (CRPS).

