### Hypotheses

Our hypotheses in the study are as follows:
One week of plaster cast immobilization may successfully be implemented at the participating hospitals with a good acceptability of the study protocol rate (small number of protocol violations).One week of plaster cast treatment (condition B) will give a lower PRWE score (less pain and better physical function) compared to the usual care group (condition A) for non-reduced DRFs.One week of plaster cast treatment (condition B) will give lower pain scores with less use of pain medication compared to the usual care group (condition A) for non-reduced DRFs.One week of plaster cast treatment (condition B) will lead to earlier optimal functional outcome scores than the usual care group (condition A) for non-reduced DRFs.One week of plaster cast treatment (condition B) will be less costly compared to the usual care group (condition A) for non-reduced DRF.There is no difference in complications for the intervention group (condition B) versus the usual care group (condition A).

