### Measurements

For this study, the following main study parameters are gathered: functional outcome, return to activity, cost-effectiveness, and acceptability of the study protocol.
Patient-reported outcome (functioning and patient satisfaction): It is known that 1 week of plaster cast for a non-reduced DRF is safe. Secondary displacement of the fracture is not significantly different with longer plaster cast treatment [8, 9]. So, the most important question is whether 1-week treatment gives better functional results and higher patient satisfaction. The best measurement method to measure patient satisfaction and functional result is using a patient-reported outcome (PRO) [14]. In addition, PROs are better predictors of participation, such as the ability to return to work or perform daily activities, than more objective clinical measures.The Patient-Reported Wrist Evaluation (PRWE) is specifically designed for wrist and hand functioning. The PRWE is a reliable and valid measure of patient-rated pain and disability for wrist conditions [15, 16]. Furthermore, a validated Dutch version of the questionnaire is available [17]. The PRWE is a measurement with a score from 0 to 100, where 0 is no wrist function problems or pain. The minimal clinical important difference for PRWE is a difference of 11 points [18].The questionnaires will be sent to the patient after 6 weeks and 3, 6, and 12 months.Return to activity will be measured using the productivity costs questionnaire (iCPQ). Questions about return to work, leisure activities, household activities, and pain will be asked. These questions will be asked after 1 and 6 weeks, 6 months, and 1 year.A cost-effectiveness analysis will be performed alongside the stepped wedge trial. The Health care Institute of the Netherlands (ZIN) 2016 guideline for economic evaluations forms the basis of the analysis [19]. Healthcare consumption from inclusion to final follow-up of the patient is measured. This is in line with the measurement pathway of the clinical study. Healthcare consumption is multiplied by unit costs associated with healthcare consumption. Also, productivity-related costs seem to play an important role. Therefore, the societal perspective is the base case. A healthcare perspective is used as the scenario. These will be measured using a selection of questions of the medical consumption questionnaire (iMCQ) and the productivity costs questionnaire (iCPQ). These questions will be asked after 1 and 6 weeks, 6 months, and 1 year. The costs and for example months not working will be compared for the two different condition groups.Acceptability of the study protocol. Measuring the actual time of plaster cast treatment and number of patients who followed the protocol. If not following the protocol (condition A or B), reason for violation of the protocol. The answers to these questions will be gathered at the end of the study by provided information from the hospitals and questions asked to the participating physicians. All patients who gave informed consent will be checked if they follow the correct protocol. If they did not follow the protocol, information will be gathered why the protocol was not followed. Additionally, questions will be asked to the participating centers (local head of research). The questions asked are about feedback to the study, if they will implement the interventional treatment, why they will or will not implement the treatment, what changes to the treatment they would make, etc. The number of protocol violations and comments will be compared for both groups.

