## Discussion

This publication presents an implementation study with the use of a randomized multicenter stepped wedge design for the use of 1 week of plaster cast immobilization after non-reduced DRF. This study will be used to implement 1 week of plaster cast immobilization in several hospitals. In addition, this study tries to answer the question whether 1 week of plaster cast gives lower PRWE scores, better patient satisfaction, earlier return to work, and lower costs and if it will have the same complication rate.

A limitation of this study is the variability in clinical judgment when to reduce a DRF and thereby the chance of bias due to the surgeon’s decision who expects a high chance of secondary displacement. However, the variability in deciding when to reduce a DRF is part of common daily practice. A second limitation may be the choice for a stepped wedge design instead of a randomized controlled trial. During the feasibility study, we encountered a lot of problems with patient cross-over, difficulty performing the study for the hospitals and a large number of patients who did not want to participate in the study. By using a stepped wedge design, we think the problems with the treatment protocol will be less variable. In addition, the greater variability in deciding when to reduce a DRF leads to the exclusion criteria which will be used in general practice. Therefore, this study will give an answer which can be directly translated into daily practice.

The strengths of this study are the pragmatic nature of this study, the fact that it is an implementation study (using the Dutch guideline) in combination with a comparative study, and the use of a cost-effectiveness analysis. The pragmatic nature of this study, using a stepped wedge design, leads to a very clear protocol to use for every hospital. A clear and easy protocol is necessary as this study is an implementation study. In addition, with this study design, we can include 440 patients in 1-year time. A cost-effectiveness analysis will be performed which will give extra evidence for the effectiveness of 1-week plaster cast immobilization. Other strengths of the study are the validated primary outcome measure (PRWE) and taking into account psychological views of post-traumatic pain using the PCS-4.

As this is an implementation study, we hope the results of this study will be used for the implementation of 1-week plaster cast immobilization for non-reduced DRF nationally.

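### Intention-to-treat is the one analysis named for every outcome, including the hypothesis of no difference in complications, where any non-adherence pulls the result towards that hypothesis

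*Protocol article*

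**What the plan says.** The Statistical analysis section closes its list of models and tests with "The analysis will be performed by using the intention-to-treat model (according to the groups to which they were originally designed". It makes no exception by outcome and names no second analysis set. Complications are among the outcomes listed: "The difference in complication rate will be determined using either a Fisher exact or a chi-square test".

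Under Hypotheses, five statements expect successful implementation or a benefit of 1 week. The sixth is of a different kind: "There is no difference in complications for the intervention group (condition B) versus the usual care group (condition A". The Discussion repeats it as a question whether the complication rate will be the same.

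On adherence, the Background describes "A feasibility study including 40 patients with a non-reduced DRF", randomised between 1 week and 4–5 weeks of cast, with "cross-over in eight patients, seven patients went from the control group to the intervention group". The Discussion gives cross-over as one reason for the present design: "By using a stepped wedge design, we think the problems with the treatment protocol will be less variable". Under Measurements, acceptability is assessed by "Measuring the actual time of plaster cast treatment and number of patients who followed the protocol", together with the reasons for violations, and the number of violations is compared between the groups. In the Statistical analysis section these data appear only here: "We will analyze the percentage of protocol violations and the willingness to participate from participating patients, hospitals, and physicians using a feedback evaluation".

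**The concern.** For PRWE and pain, where the plan hopes to show a benefit, patients who get the other condition's cast time make that benefit harder to show. Intention-to-treat is then conservative. For complications the plan hopes to find no difference, and the same patients make the two conditions look more alike. One rule therefore guards against a false claim for some hypotheses and leans towards the claim for another.

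What is at stake is the safety statement. The Oversight section provides for no interim analysis and no data monitoring board, so the final comparison carries the conclusion on complications. The Discussion hopes the results will be used for national implementation. The trial is open, and under Investigational treatment condition A patients attend the clinic at 1 week, the point at which condition B patients have the cast removed, so some departure from the assigned condition is plausible.

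**Working it through.** **The plan's own figures.** The article gives no sample size, rate or margin for complications. Its only calculation is for PRWE. Table 1 has 55 condition A and 55 condition B cluster-periods, 110 in all: 110 × 3 = 330 and 110 × 4 = 440, as stated. The stated power of 0.85 for 35 v 25 points with ICC 0.01 is reproduced by a standard stepped-wedge variance (fixed periods, random cluster effect) if the SD is about 20, which the article does not state. The 440 patients split into 55 × 4 = 220 per condition. After the protocol's 30% loss, 220 × 0.7 = 154 remain.

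**Dilution.** Let pA and pB be the complication rates under the long and the short cast, cA the share of A patients treated as B, and cB the reverse. Under intention-to-treat:

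- observed A = (1 − cA)·pA + cA·pB
- observed B = (1 − cB)·pB + cB·pA
- observed difference = (1 − cA − cB)·(pB − pA)

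**Assumptions, none from the article:** pA = 10% and pB = 20%; two-sided 5%; clustering and period ignored, as the planned Fisher or chi-square test does.

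**Power without cross-over.** The mean rate is 15%. The null standard error is √(0.15 × 0.85 × 2/220) = 0.0340. The standard error under the alternative is √((0.09 + 0.16)/220) = 0.0337. Power = Φ((0.10 − 1.96 × 0.0340)/0.0337) = 0.84.

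**Scenarios.**

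| cA / cB | Share kept | Observed A v B | Power, 220 per condition | Power, 154 per condition |
|---|---|---|---|---|
| 0 / 0 | 1.00 | 10.0% v 20.0% | 0.84 | 0.69 |
| 10% / 2% | 0.88 | 11.0% v 19.8% | 0.73 | 0.57 |
| 20% / 5% | 0.75 | 12.0% v 19.5% | 0.58 | 0.44 |
| 35% / 5% | 0.60 | 13.5% v 19.5% | 0.40 | 0.29 |

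The last row is the feasibility pattern, 7/20 = 35% and 1/20 = 5%, if its 40 patients were split 20/20. The article does not give the arm sizes.

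**Other assumed rates, 220 per condition.** For 5% v 12%, power goes from 0.75 with no cross-over to 0.49 at 20%/5% and 0.32 at 35%/5%. For 15% v 25% it goes from 0.75 to 0.49 and 0.33. The pattern is the same.

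**Would a margin alone cure it?** Take an illustrative 10-point margin (not in the article) and a true excess equal to it, 10% v 20%, with 220 per condition. The chance of wrongly concluding that 1 week is no worse is 2.5% with full adherence, 4.8% at 10%/0%, 10.8% at 20%/5% and 20.4% at 35%/5%. A margin is needed, but it does not remove the dilution.

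**The case against.** Five objections deserve a fair hearing.

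1. **The section does not exclude other analyses.** A reader might infer that intention-to-treat is the wrong choice, or that any supportive analysis is ruled out. The documents support neither. Intention-to-treat suits an implementation trial, where the effect of a hospital adopting the protocol matters, and a supportive set may stand in an analysis plan that is not shown. What stands is that the article fixes one rule for all outcomes next to a no-difference hypothesis and its own record of cross-over.

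2. **The feasibility rate belongs to another design.** A reader might infer that 35%/5% cross-over is to be expected here. It is not. The feasibility study randomised patients individually. Here patients follow their hospital's condition (Randomization), and even those who decline consent are treated by it (Investigational treatment). This objection stands in full: that row is an upper scenario.

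3. **Measuring violations is not expecting them.** The first hypothesis anticipates a small number. This also stands.

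4. **An as-received comparison can mislead in the same direction.** If wrists judged at higher risk are kept longer in cast, complications move into the long-cast group and 1 week looks safer. Adjustment for age and fracture class need not remove this. This stands, and it limits what a supportive analysis can show.

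5. **Non-significance is not similarity.** Two non-significant tests do not show that complications do not differ, in any analysis set. This stands too, and is the more basic weakness, so the conclusion has to rest on confidence intervals.

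**Conclusion.** The concern holds in a limited form. The direction is certain: with intention-to-treat alone, any non-adherence shrinks the complication contrast by (1 − cA − cB), towards the hypothesised result. The size is unknown, because the article gives no complication rates, no margin and no expected adherence for this trial.

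Under the assumed 10% v 20% and 220 per condition, mild cross-over of 10%/2% raises the chance of missing a doubling of complications from 16% to 27%. A miss of 60% (power 0.40) needs both the assumed doubling and the feasibility-study pattern with assumed equal arms. It should not be read as a forecast.

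Complications are a secondary outcome and the data needed are already collected, so this is a moderate point that is cheap to address. It is no reason to abandon intention-to-treat.

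**What to change.** - Keep intention-to-treat as the principal analysis for every outcome, and as it stands for the superiority hypotheses.
- For complications only, pre-specify a supportive analysis that accounts for the cast time already recorded: per-protocol or as-received, adjusted for age and fracture class.
- Ideally add an adherence-adjusted estimate that uses the cluster's assigned condition as instrument. It keeps the link to the randomised switch and in effect divides the intention-to-treat difference by the share kept. In the 10%/2% scenario that is 8.8/0.88 = 10.0 points. The interval widens accordingly.
- Report the intention-to-treat and the supportive results as differences in complication rate with confidence intervals. State beforehand what excess would be relevant, and claim similar rates only if neither interval includes it.

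**Cost.** One extra analysis, no new data, and a statement of the relevant excess. Requiring both intervals makes the claim of similarity harder to reach. The as-received estimate is open to selection that can also favour 1 week, so it is supportive only and cannot by itself establish safety.
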